### Implementation framework (dynamic adaptation process–DAP)

At the time of writing, the Preparation Phase has been completed, including qualitative data collection and preliminary adaptation recommendations. The Adaptation Phase is underway, while the Implementation and Evaluation Phases will take place during the randomized pilot trial.

### Preparation phase (year 1)

#### Overview

Multiple data sources guide the adaptation of the IPS model. Using an implementation science framework previously applied by the US team [16, 30], we identified four key domains for adaptation: systemic, organizational, provider, and participant levels. Our goal is to assess contextual factors and organizational readiness for implementing evidence-based practices in Jalisco. We use a framework developed in prior Latin American studies to document implementation barriers and facilitators [31, 32].

#### Data collection

Systemic level: we conducted six semi-structured interviews with influential policymakers overseeing current mental health policies in Jalisco, focused on potential adjustments to align IPS within the mental health system, state legislation, and labor market. We included The National Employment Service to gather insights on employability for people with disabilities, including mental health conditions. We also explored how policymakers perceive the potential of IPS to meet local needs.Organizational level: we interviewed five health managers to examine the conditions required to implement and sustain IPS. Topics included existing resources, anticipated challenges, and strategies to integrate IPS into public services in Jalisco.Provider level: two focus groups with mental health providers (6–8 per group) discussed current practices, training needs, and the structure of existing supported employment services. The discussions addressed pragmatic factors (e.g., staffing, funding), organizational culture (e.g., leadership), and coordination with other public sectors.Participant level: we held two focus groups of people with SMI and two with family members (6–8 participants each) to explore the perceptions of IPS acceptability and identify ways to adapt the model to meet users’ needs.

## Data analysis

We analyzed the interview and focus group data using a flexible coding approach [33, 34], as applied in prior work by the US team in Latin America [31, 32]. This process included audio recording and professional transcription. The analytic process began with a priori codes informed by the multilevel structure of the interview guides (systemic, organizational, provider, participant), followed by the identification of emergent codes during transcript review. Coding was performed by multiple team members who met regularly to refine the codebook and resolve discrepancies through consensus. We then organized coded excerpts into a matrix aligned with the four implementation levels to facilitate comparison across stakeholder groups and to identify salient barriers and facilitators.

### Adaptation phase

The Research Adaptation Team reviews recommendations from the previous phase and incorporates proposed modifications to the IPS model. These recommendations are based on contextual findings, including how local factors may influence the intervention curriculum and considerations for potential scale-up. The team includes Spanish-speaking trainers from the US, local trainers, and the core research group, with regular participation from health managers, service providers, and study consultants (e.g., policymakers). These stakeholders do not formally adopt the IPS model; rather, they contribute to its adaptation by identifying contextual barriers and facilitators. Their insights help inform implementation strategies that preserve fidelity to core IPS principles while ensuring cultural and systemic relevance in the Jalisco context.

Following methods used in prior Latin American studies that adapted evidence-based practices [31, 32]. Twice a month meetings follow a participatory group discussion format to align the intervention with the Jalisco context and support its operational translation. IPS trainers in New York contribute insights on implementation challenges observed in similar contexts. The team systematically reviews intervention materials and discusses lessons learned from international experiences, in collaboration with IPS Center leaders. They make decisions regarding content, delivery strategies, and objectives to preserve the fidelity of core IPS elements during adaptation. The team identified required modifications to support local implementation, which may include adjustments to the training process, content delivery, language, and modality [15].

### Implementation phase

The Research Adaptation Team, in coordination with the IPS Center, identifies and trains IPS Employment Specialists affiliated with the National Employment Service in Jalisco. These specialists participate in a 4-day, in-person training that introduces the IPS model, followed by structured technical assistance. Support includes individual and group supervision, case consultations, and sessions addressing specific topics requested by participants. Role-specific calls are scheduled biweekly during the first 6 months and then shift to a monthly format, with additional meetings organized as needed.

During the Implementation Phase of the randomized pilot trial, monthly consultation calls focus on team operations. A learning management system provides access to training modules, event registration, module completion tracking, attendance records, and evaluation tools, following the model established by the IPS Center in New York. The Research Adaptation Team and IPS Center representatives continue to deliver training to support local adaptations, adjust instructional content, and address emerging barriers to implementation (e.g., staff shortages, stigma).

To manage challenges, the team uses a structured problem-solving approach informed by prior experience, local knowledge, and relevant literature. External experts participate in specific meetings when issues arise that require additional technical, contextual, or cultural expertise. These experts include IPS trainers from the IPS Center in New York, implementation science specialists, and local consultants with experience in disability rights, labor inclusion, gender and sexual diversity, and youth mental health. Their input is sought in situations where emerging barriers relate to cultural or social factors that can influence engagement in employment, such as stigma related to mental illness, gender roles in the workplace, discrimination based on sexual orientation, or limited economic opportunities for young adults. This tailored consultation process supports context-sensitive problem-solving and helps ensure that IPS implementation remains aligned with both core model principles and local cultural dynamics.

### Evaluation phase

This phase assesses how IPS is implemented in practice and identifies barriers and facilitators that emerge during real-world delivery. Mixed-methods data will be collected at approximately 6 and 12 months from key stakeholders, including participants, IPS Specialists, clinical staff, and administrators. Qualitative interviews will explore experiences with implementation, perceptions of acceptability and feasibility, and contextual factors influencing the adoption of IPS principles. Quantitative indicators, including fidelity scores and service-level metrics, will complement the qualitative findings. All implementation data will be organized across four levels—systemic, organizational, provider, and participant—to allow structured comparison and to capture how challenges and adaptations evolve over time.

### Data collection

Systemic level: five semi-structured interviews with influential policymakers in Jalisco.Organizational level: five semi-structured interviews with health managers in the Jalisco mental health system.Provider level: two focus groups with provider staff (both involved and not involved in providing IPS) exploring acceptance or resistance to the model. The discussion follows a funnel structure, starting from general perceptions and narrowing toward concrete, locally relevant examples.Participant level: two focal groups with PSMI (*n* = 6–8) and one with family members (*n* = 6–8), exploring perceptions of IPS acceptability and the role of families in recovery-oriented activities.

## Data analysis

As in the Preparation Phase, qualitative data from the Evaluation Phase will be analyzed using a flexible coding approach. Transcripts will first be reviewed using the existing multilevel codebook (systemic, organizational, provider, participant), with additional inductive codes added as needed. Coded excerpts will then be transferred into a structured matrix to compare implementation experiences across stakeholder groups and to identify patterns related to barriers, facilitators, and adaptations. This analytic strategy enables triangulation across data sources and supports the development of a heuristic model to inform future IPS implementation in Mexico.

### Monitoring

#### Data monitoring and reporting

The coordinating center, composed of the Principal Investigator, study coordinators, research staff, data analyst, and statistician, will hold monthly meetings to oversee daily trial operations. These include participant enrollment, data collection, intervention delivery, and compliance with regulatory requirements. An external steering committee, including experts in psychiatry, psychosocial rehabilitation, biostatistics, and mental health advocacy, will convene quarterly to review study progress and participant safety. This committee is independent of the sponsor and study team, and will provide guidance on trial continuation, protocol modifications, or early termination, based on safety indicators and study performance.

If the National Institute of Mental Health (NIMH) does not assign a Data and Safety Monitoring Board (DSMB), an independent board of local experts in Mexico will assume this role. No formal interim efficacy analyses are planned, as this is a feasibility study. However, the DSMB will review the final Data Safety Monitoring Plan, study protocol, protocol amendments, reportable adverse events, and annual progress reports.

#### Adverse event reporting and harms

The latest version of the REDCap system will be used to document both scheduled assessments and unscheduled (anytime) events, including adverse events. If a participant shows signs of psychological or emotional distress, the assigned psychiatrist at the Center for Comprehensive Care in Long-Stay Mental Health will be notified by the research team. When necessary, an immediate and supervised referral will be arranged to address concerns about potential self-harm. Research staff will be trained to recognize indicators that require urgent clinical attention, such as agitation, aggression, tearfulness, fear, anger, suicidal ideation, or worsening psychiatric symptoms. All adverse events and actions taken will be documented and reviewed periodically by the DSMB.

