#### Risk and risk management

Participants will be adults with SMI receiving community-based services; therefore, some level of clinical and psychosocial risk is expected. A structured risk management protocol will be implemented to ensure participant safety throughout the trial. All IPS Employment Specialists and research staff will be trained to identify warning signs related to clinical deterioration, including increased symptoms, functional decline, suicidal ideation, or psychosocial crises.

If a participant reports suicidal thoughts, expresses intent, or presents significant behavioral changes suggesting elevated risk, the IPS Employment Specialist will pause all study-related activities and immediately activate the clinical escalation protocol. This protocol includes: (1) notifying the participant’s treating psychiatrist or mental health provider; (2) conducting a brief safety check using established procedures from local mental health services; and (3) coordinating a same-day clinical evaluation when indicated. In emergency situations, specialists will contact emergency services according to institutional guidelines.

Study participation may be temporarily paused or discontinued if the participant experiences acute psychiatric decompensation, requires hospitalization, or if the clinical team determines that continued involvement poses an unacceptable risk. All risk events and procedures will be documented and reviewed by the Research Adaptation Team and the site’s clinical supervisors to ensure consistent application of risk management procedures. The protocol prioritizes continuity of clinical care, and all participants will remain within their routine mental health services regardless of trial involvement.

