#### Outcomes

This study will assess feasibility outcomes related to the implementation of the IPS model and explore its preliminary effects on participant employment, financial well-being, and health-related outcomes. The evaluation will emphasize feasibility outcomes, while participant-centered outcomes will provide additional insight into the model’s potential impact. Data will be collected at baseline and through quarterly follow-up interviews. All instruments will be administered in Spanish; if no validated Spanish version exists, the measure will be translated using forward–back translation by bilingual specialists, followed by expert panel review to ensure conceptual equivalence and linguistic clarity. Table 3 provides a detailed summary of all planned outcomes and associated measures.

**Table 3 Tab3:** Outcomes and measures

Measure	Data Source	Interval (duration)	Constructs Addressed
Baseline participant interview	Participant	Baseline (45–60 min)	- Demographics (age, sex, gender, marriage status, race/ethnicity)—employment history (past year and past 5 years)—income history (annual income, income sources)—Housing history (past 5 years)—health service utilization history (past-year hospitalization and emergency service utilization, regular medical care)—health and functionality (Brief Psychiatric Rating Scale (BPRS), Medical Outcomes Study Short-Form 12-Item (SF-12, mental and physical), Social Occupational Functioning Scale (SOFS), Recovery Assessment Scale (RAS-24)—Social capital (numbers, education, and justice system involvement of parents, siblings, children, and friends)—Justice system involvement (arrest, incarceration, and conviction history)
Quarterly employment interview	Participant	Quarterly (10 min)	- Past-quarter employment (any competitive employment; per-job weeks worked, hours worked per week, hourly wage, job start/end dates if applicable)
Follow-up participant interview	Participant	6, 12 months (40–50 min)	- Housing (past 6 months)—health service utilization (past 6 months hospitalization and emergency service utilization)—health and functionality (Brief Psychiatric Rating Scale (BPRS), Medical Outcomes Study Short-Form 12-Item (SF-12, mental and physical), Social Occupational Functioning Scale (SOFS), Recovery Assessment Scale (RAS-24)

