#### Assignment of interventions: blinding

Due to the nature of the intervention, it is not feasible to blind participants, clinical staff delivering IPS, or the research team involved in its implementation. However, interviewers conducting baseline and follow-up quantitative assessments—covering employment, hospitalization, symptoms, functioning, and quality of life—will remain blinded to group assignment. Data analysts and statisticians will also be blinded during the analysis phase.

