### Data collection and management

#### Plans for assessment and collection of outcomes

Baseline structured interviews will be conducted prior to randomization to collect data on demographic characteristics, social capital, physical and mental health status, health service utilization, justice system involvement, functionality, and employment and financial history [21]. Validated instruments with established psychometric properties and Spanish versions will be used at baseline and follow-up assessments. These include the Brief Psychiatric Rating Scale (BPRS) for psychiatric symptoms [22], the Medical Outcomes Study Short-Form 12-Item (SF-12) for physical and mental health [23], the Social and Occupational Functioning Scale (SOFS) for functioning and role performance [24], and the Recovery Assessment Scale (RAS-24) to assess perceived recovery and empowerment [25]. All instruments will be administered by trained research staff using structured protocols to ensure consistency and data quality.

Quarterly structured follow-up interviews will assess employment status during the prior 3 months. Data collected will include job titles, employment dates, hours worked, and wages earned. When applicable, the reason and timing of job termination will also be recorded [21]. These structured interviews will be conducted in person at the Center for Comprehensive Care in Long-Stay Mental Health, subject to public health restrictions. If a participant is unavailable, the research team will make multiple contact attempts within the same data collection window. Missed interviews will be documented, and retrospective data will be gathered at the next opportunity.

Follow-up structured research interviews scheduled at 6- and 12 months after randomization, the follow-up interviews will augment the quarterly employment interviews and include measures of health and functionality mirroring those administered at baseline. Additional data collected describes housing, social capital, and health service utilization [21]. Follow-up interviews will be conducted at the same time as the corresponding quarterly employment interviews. As with the quarterly employment interviews, when participants are unavailable for follow-up interview, the research assistant will make several efforts to track and schedule the interview within the designated time until the next quarterly interview period.

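### Between months 6 and 12 visits, harms that do not lead to hospital are described as recorded when staff notice them, with one more trained observer in the IPS arm; a brief identical quarterly enquiry would narrow this gap

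*Protocol article*

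**What the plan says.** **Recording of harms.** Under Adverse event reporting and harms, REDCap is to "document both scheduled assessments and unscheduled (anytime) events, including adverse events". The same section has research staff trained to recognise urgent signs, and the research team notifying the assigned psychiatrist when distress is seen. It describes no standard question about adverse events.

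**What both arms are asked, and when.** Table 3 gives the content of the quarterly interview as "Past-quarter employment (any competitive employment; per-job weeks worked, hours worked per week, hourly wage, job start/end dates if applicable", with a length of 10 minutes. The 6- and 12-month follow-up interview adds "health service utilization (past 6 months hospitalization and emergency service utilization", together with BPRS, SF-12, SOFS and RAS-24. Under Plans for assessment and collection of outcomes, the follow-up interviews take place at the same time as the corresponding quarterly interviews. On the quarterly interviews that section says "These structured interviews will be conducted in person at the Center for Comprehensive Care in Long-Stay Mental Health", and "Missed interviews will be documented, and retrospective data will be gathered at the next opportunity". The blinding section keeps interviewers blind for assessments "covering employment, hospitalization, symptoms, functioning, and quality of life".

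**Who observes.** Risk and risk management says "All IPS Employment Specialists and research staff will be trained to identify warning signs". It then names only the Employment Specialist as the person who stops study activity and starts the escalation steps.

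**Who reviews.** Under Data monitoring and reporting, an external steering committee reviews participant safety each quarter and advises on continuation, and a DSMB reviews reportable adverse events and a Data Safety Monitoring Plan.

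**The concern.** When harms are recorded because someone noticed them, the record depends on how many people are looking. Both arms share the clinical team and the trained research staff. Only the IPS arm also has an Employment Specialist, who is trained to spot deterioration and cannot be blinded. With equal true risk, the IPS arm would tend to show more recorded events of the kind that produce no hospital or emergency visit: suicidal ideation, psychosocial crises and moderate worsening.

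At stake is the quality of the safety information that the steering committee and the DSMB work from, both its timing and its balance between arms. An apparent excess in the IPS arm could be partly a matter of closer observation, and a problem in a usual-care participant could come to light later. A side issue is that the escalation text applies to any participant but gives the first step to a role that does not serve usual-care participants.

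**Working it through.** The plan states no adverse event rate or detection figure, so there is nothing to reproduce. The check is of the schedule, then of burden, then an illustration.

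**1. Scheduled interviews common to both arms (Table 3; Plans for assessment and collection of outcomes)**

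| Month | Employment | Hospital and emergency use | BPRS and other scales |
|---|---|---|---|
| 3 | yes | no | no |
| 6 | yes | past 6 months | yes |
| 9 | yes | no | no |
| 12 | yes | past 6 months | yes |

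- Interviews with any listed health question: 2 of 4.
- Interviews for which Table 3 names a question on suicidal ideation or crisis: 0 of 4. The BPRS at months 6 and 12 may touch on it; its items are not listed.
- Longest interval between listed health questions: 12 − 6 = 6 months now, 6 − 3 = 3 months if months 3 and 9 are used. This is spacing of questions. It is not time to detection, because clinicians see participants throughout.

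**2. Observers by arm**

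- Both arms: clinical team (Relevant concomitant care) and trained research staff.
- IPS arm only: the Employment Specialist. The monthly IPS Participation Measure is not counted as a detection channel, since Table 3 lists no adverse event item on it.

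**3. Burden of the enquiry (full attendance)**

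- Suicidal ideation or crisis at all four interviews: 120 × 4 = 480 enquiries, or 160 × 4 = 640 if 160 are enrolled, as Sequence generation states.
- Hospital and emergency questions at months 3 and 9 only: 120 × 2 = 240, or 160 × 2 = 320.
- Time at an assumed 2 minutes per interview (range 1 to 3): 480 × 2 / 60 = 16 hours (8 to 24); 640 × 2 / 60 = 21.3 hours (10.7 to 32.0). Months 6 and 12 need fewer questions, so this leans high.
- Relative to a 10-minute interview: 2/10 = 20% (10% to 30%).

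**4. Illustration of direction (every input assumed)**

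Let true risk be equal in the arms, *s* the chance that shared observers record an event (0.3 to 0.5), *e* the independent extra chance from the Employment Specialist (0.2 to 0.4), and *q* the sensitivity of the common enquiry (0.6 to 0.8). The true risk cancels.

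- Recorded IPS:control ratio without the enquiry = [1 − (1 − s)(1 − e)] / s. Lowest, s = 0.5 and e = 0.2: 0.60/0.50 = 1.20. Highest, s = 0.3 and e = 0.4: 0.58/0.30 = 1.93.
- With the enquiry, all sources pooled = [1 − (1 − s)(1 − q)(1 − e)] / [1 − (1 − s)(1 − q)]. Lowest, s = 0.5, q = 0.8, e = 0.2: 0.92/0.90 = 1.02. Highest, s = 0.3, q = 0.6, e = 0.4: 0.832/0.72 = 1.16.
- Solicited events only: q/q = 1.00, provided attendance and candour are equal in both arms.

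So the enquiry shrinks the imbalance and does not remove it while spontaneous reports are pooled in. The ratios show direction only and are not estimates for this trial.

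**The case against.** The strongest reply is that no error has been shown. How adverse events are solicited usually belongs in a safety plan; the article names such a plan and does not reproduce it. Table 3 lists outcomes and is not a safety schedule, so its silence does not prove that nobody asks. This stands, and it limits the point to a recommendation on the schedule as described.

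A second reply is that much is already covered. Blinded interviewers ask both arms about hospital and emergency use for the whole year and score symptoms and functioning at months 6 and 12. The month 3 and 9 interviews are in person, research staff are trained to recognise signs, and both arms keep the same clinical services. This also stands. What is left exposed is a small class of events and the timeliness of information between the six-monthly visits.

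Readers might infer three stronger things, and the document supports none of them:

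- *That a planned result is biased.* Statistical methods for primary and secondary outcomes plans no between-arm adverse event analysis.
- *That usual-care participants have no escalation route.* The adverse event section has the research team notify the psychiatrist for any participant and arrange supervised referral when needed. Only the wording of the risk section is narrower.
- *That an identical enquiry would close the gap.* It equalises solicited events only.

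**Conclusion.** The point holds as a modest design improvement. On the stated schedule, two of the four interviews common to both arms carry no health question, none is listed as asking about suicidal ideation or crisis, and one arm has an extra trained and unblinded observer. Oversight bodies that review safety may therefore receive later and less balanced information on harms short of hospital.

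The size of any imbalance cannot be derived, because the document gives neither event rates nor detection probabilities. The conclusion rests on Table 3 being the full content of the interviews and on the Data Safety Monitoring Plan not already requiring such questions. If it does require them, what remains is to bring Table 3 and the risk section into line with it. The pilot's feasibility aims are not affected.

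**What to change.** - **(a) Common enquiry.** Have the blinded interviewer ask both arms the same brief questions: suicidal ideation or crisis at all four quarterly interviews; hospitalisation and emergency visits at months 3 and 9 only, because months 6 and 12 already ask about them. After a missed interview, ask about the period since the last completed one, as the plan already does for employment. Record event dates so that no event is counted twice against the six-month recall items.
- **(b) Flag the route of detection.** Add an arm-neutral field, solicited at the common interview or spontaneous, which blinded analysts can see. Keep the detailed source restricted, since an entry naming the Employment Specialist reveals the arm and the plan says "Data analysts and statisticians will also be blinded during the analysis phase". Base any by-arm safety statement on solicited events, and show spontaneous ones separately.
- **(c) Escalation wording.** In Risk and risk management, name research staff alongside Employment Specialists as activators for participants in either arm, in line with the adverse event section. The clinical content of the steps stays with the clinicians.

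**Cost.** A few short questions at visits that already take place (about 2 minutes each, assumed), two REDCap fields, one with restricted access, and one sentence. Interviewers must be ready to act on a positive answer about suicidality, and an ethics amendment may be needed. The Trial status section says recruitment has not begun, so the change is cheapest now.
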